
Taken together, two hypotheses can be put forward. A colloid-based goal-directed individualized fluid therapy using HES may improve outcome compared to 0.9 % saline or may promote postoperative organ dysfunction and reduced survival in moderate-to-high risk patients undergoing major surgery. The large number of patients for whom the question applies each year worldwide, current concerns about the risks related to the use of HES-based products in surgical patients, and the cost differences between HES and 0.9 % saline indicate the importance of evaluating the benefit/risk balance of these products and of evaluating the influence of the type of solution administered for the correction of hypovolemia during surgery on postoperative outcomes.

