Secondary outcome measures will be as follows:Postoperative complications evaluated separately within 14 days:Kidney dysfunction: oliguria (24-h urine output < 500 ml), KDIGO score(KDIGO categories [39]:KDIGO stage 1: increase in serum creatinine × 1.5 to 1.9 OR ≥26.5 μmol/l from baseline OR urine output <0.5 ml/kg/h for 6 to 12 hKDIGO stage 2: increase in serum creatinine × 2.0 to 2.9 from baseline OR urine output <0.5 ml/kg/h for ≥12 hKDIGO stage 3: increase in serum creatinine × 3.0 from baseline OR ≥353 μmol/l OR initiation of renal replacement therapy OR urine output <0.3 ml/kg/h for ≥24 h OR anuria ≥12 h)Cardiovascular complications: cardiac arrhythmia, acute heart failure, myocardial infarction, or pulmonary embolismPulmonary complications: postoperative hypoxemia, postoperative pneumonia, need for intubation and invasive mechanical ventilation or postoperative noninvasive ventilation, postoperative ARDS, and days alive without ventilation (ventilator-free days)Postoperative systemic inflammatory response syndrome (SIRS) score [40]Infectious complications: surgical site infection, intra-abdominal abscess, postoperative peritonitis, sepsis, severe sepsis or septic shockSurgical complications: anastomotic leak, reoperation or endoscopic drainageSepsis-related organ failure assessment (SOFA, modified from [41], see Additional file 2) score (excluded Glasgow Coma Score)Total fluid volume (0.9 % saline and HES 130/0.4) administered during the surgical period and the first 24 postoperative hoursVolume of blood loss and number of units of packed red blood cells administered during the operative period and the first 24 postoperative hoursTime to return of bowel function (flatus and stool)Unexpected ICU admission (or readmission) within 28 days following surgeryDuration of hospital stay: high dependency unit (HDU), intensive care unit (ICU), hospital stayAll-cause mortality at Day 28 and 3 months

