### Safety

All adverse events thought to be related to the trial fluids will be reported to the trial coordinating center. According to the French Public Health Code, all suspected unexpected serious adverse events will be reported to the ANSM. In addition, this information will be submitted to the data monitoring and safety committee (DMSC). The DMSC is independent of the trial investigators and will perform an ongoing review of safety parameters and overall study conduct. The DMSC is comprised of two independent experts in large-scale clinical trials and one independent statistician.

The DMSC will be responsible for safeguarding the interests of trial participants, assessing the safety and efficacy of the interventions during the trial, and for monitoring the overall conduct of the clinical trial. To contribute to enhancing the integrity of the trial, the DMSC may also formulate recommendations relating to the recruitment/retention of participants, their management, improving adherence to protocol-specified regimens and retention of participants, and the procedures for data management and quality control. The DMSC will provide recommendations about stopping or continuing the trial to the Steering Committee (SC) of the FLASH trial. Stopping rules will be based on the following:Group-difference in all causes mortality orGroup-difference in postoperative AKI (requirement for renal replacement therapy)

The DMSC will be advisory to the SC. The SC will be responsible for promptly reviewing the DMSC recommendations, to decide whether to continue or terminate the trial, and to determine whether amendments to the protocol or changes in trial conduct are required.

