### Statistics

Analysis will be by intention-to-treat (ITT) on data from the modified-ITT population (see Additional file 3). Unadjusted chi-square test or Fisher’s exact test will be used for the primary outcome analysis. Adjusted analysis will be conducted with the use of robust random effects Poisson generalized-linear regression (1) to take into account adjustment on possible confounding covariates selected according to clinical relevance and stratification variables and (2) to consider within and between center variability. Data will be presented as relative risks and 95 % confidence intervals.

Regardless of the results from the analysis of the composite outcome, each component of the composite primary outcome measure will be also analyzed separately using similar methods as described for the primary analysis. The Hochberg procedure will be used to adjust for multiple testing of components of the composite primary outcome. A chi-square test (or Fisher’s exact test, as appropriate) will be used for secondary binary outcomes. Continuous variables will be compared with the use of the unpaired *t*-test or Mann–Whitney *U* test as appropriate. The Shapiro-Wilk test will be used to assess homoscedasticity. Adjusted analyses will be performed using the same adjustments variables. Time-to-event curves will be calculated with the use of the Kaplan-Meier method. Longitudinal analysis using mixed models will be used to take into account within and between subject variability.

Per protocol analyses will be performed on the primary outcome and the most important secondary outcomes. Missing data will be handled in accordance with the multiple imputation method (STATA command mi) if missing data are greater than 5 % [42].

A total of 2 × 413 patients will be needed to have 95 % power to show an absolute between-group difference of 10 % in the primary outcome measure at a two-sided alpha level of 0.05, assuming a 5 % mortality rate and 20 % morbidity at 14 days after surgery (thus, 25 % for the composite endpoint). Data from the literature have shown that postoperative mortality ranges from 4 % in patients undergoing elective noncardiac surgery to 20 % in those undergoing emergency abdominal surgery [1, 2, 43], with an average rate of postoperative complications following major abdominal surgery of 20 to 40 % [3, 4].

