From randomization to postoperative Day 1 (07.59 AM): total volume of trial fluids (aliquots of 250 ml); use (Y/N) and total volume of 0.9 % saline (if volume of trial fluid greater than 30 ml/kg); total number blood products and blood losses; need for mechanical invasive- or non-invasive ventilation; hourly values of blood pressures and urine output; need for administration (Y/N); and infusion rate of vasoactive drugs.

Daily from postoperative Day 1 (08.00 AM) to Day 7 after surgery (or hospital discharge):Postoperative care pathway (surgical ward Y/N, HDU Y/N, and ICU Y/N)Epidural analgesia Y/NDaily volume of trial fluid (only on postoperative Day 1) and maintenance fluids including oral and parenteral nutrition, urine output and calculated fluid balanceDaily lowest values for heart rate, blood pressure, peripheral O2 saturation, respiratory rate, temperatureBlood glucose levelResults of samples of plasma creatinine and creatinine clearance, plasma lactate, CRP, bilirubin (standard laboratory values)SIRS scoreKDIGO scoreVariables for SOFA scoring not covered above (until Day 5)Postoperative complications (Y/N, type, and date of diagnosis)Unexpected ICU admission Y/NLength of stay in HDU, ICU, and surgical wardDate of hospital dischargeDeath (Y/N and date)

Fourteen days after surgery:Postoperative complications (Y/N, type, and date of diagnosis)Need for renal replacement therapy on that day Y/N, and total days of RRT (between first and last treatment session)Unexpected ICU admission (Y/N, date of admission)Length of stay in HDU, ICU, surgical wardDate of hospital discharge (as obtained from hospital notes)Survival status (If the patient is deceased, date of death)

If the patient is still present on Day 14, follow up will continue until hospital discharge.

Twenty-eight days after surgery:Postoperative complications (Y/N, type, and date of diagnosis) from Day 14 to Day 28 after surgerySurvival status

Ninety days after surgery:Survival status (if the patient is deceased, date of death)

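### Length of stay is compared with no rule for in-hospital deaths, so if mortality differs the comparison mixes stay with death, in a direction set by when deaths occur (low severity)

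*Protocol article*

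**What the plan says.** Outcomes (protocol article) lists the time spent in hospital, ICU and HDU among the secondary outcomes, with no statement of how a patient who dies in hospital is counted. In the same list, ventilation is measured as "days alive without ventilation (ventilator-free days"), which gives a dead patient no credit.

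Statistics gives one comparison rule by variable type: "Continuous variables will be compared with the use of the unpaired" *t*-test or the Mann–Whitney *U* test. Length of stay is not named there, but this is the natural rule for it. The section also says "Time-to-event curves will be calculated with the use of the Kaplan-Meier method", without tying that method to an outcome, and names no competing-risk method.

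Death is one of the outcomes the trial worries about. Background puts forward that HES "may promote postoperative organ dysfunction and reduced survival", and Safety names "Group-difference in all causes mortality" as a basis for stopping. The sample size is set "assuming a 5 % mortality rate and 20 % morbidity at 14 days after surgery".

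**The concern.** Death ends a hospital stay. Under a *t*-test or rank test on raw days, a patient who dies on day 3 has one of the best values in the trial. If mortality is equal in the two arms this does little harm. If it differs, which is one of the stated hypotheses, a difference in raw stay can come from deaths, from slower or faster recovery, or from both, and the test cannot separate them.

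What is at stake is the reading of one family of secondary outcomes in a benefit/risk comparison. A fluid that caused early deaths could appear neutral or favourable on length of stay. The outcome list already avoids this for ventilation, so the two kinds of duration are handled inconsistently.

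**Working it through.** **Plan's own figure.** The protocol gives no figure for length of stay, so the group size is checked and then used. With 25 % versus 15 %, two-sided 0.05, power 95 % and pooled variance:

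n = [1.960·√(2·0.20·0.80) + 1.645·√(0.25·0.75 + 0.15·0.85)]² / 0.10² = (1.109 + 0.923)² / 0.01 ≈ 413 per arm. This matches.

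**Inputs.** From the protocol: 413 per arm; 5 % mortality. Assumed, because the protocol gives nothing: 10 % mortality in arm B; survivor stay log-normal, median 10 days, log-SD 0.6, the same in both arms; several patterns of death timing. Where death time is log-normal, its log-SD is 0.8.

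**Formulas.** Let q be the chance that a randomly chosen in-hospital death occurs sooner than a randomly chosen survivor is discharged.

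- Chance that a random B patient has a shorter stay than a random A patient: 0.5 + (0.10 − 0.05)(q − 0.5).
- Standard error of that estimate under the Mann–Whitney null: √[(2n+1)/(12n²)] = √[827/(12·413²)] = 0.0201.
- Shift in mean stay (B − A): 0.05 × (mean death day − mean survivor stay), where mean survivor stay = 10·exp(0.6²/2) = 11.97 days.
- For log-normal death times with median m: q = Φ(ln(10/m)/√(0.6² + 0.8²)) = Φ(ln(10/m)), and mean death day = m·exp(0.8²/2) = 1.377m. For uniform death times, q is the survivors' still-in-hospital proportion averaged over the interval.

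For m = 3: q = Φ(1.204) = 0.886; 0.5 + 0.05·0.386 = 0.519; 0.0193/0.0201 = 0.96 standard errors; chance of a significantly shorter stay in B = P(Z > 1.96 − 0.96) ≈ 16 %. The other rows follow in the same way.

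| Death timing | q | Mean shift, days | B significantly shorter: formula / simulated | B significantly longer: formula / simulated |
|---|---|---|---|---|
| Log-normal, median day 3 | 0.886 | −0.39 | 16 % / 14 % | 0.2 % / 0.3 % |
| Log-normal, median day 6 | 0.695 | −0.19 | 7 % / 8 % | 0.7 % / 0.5 % |
| Uniform, days 1–14 | 0.679 | −0.22 | 6 % / 6–7 % | 0.8 % / – |
| Log-normal, median day 10 | 0.500 | +0.09 | 2.5 % / 2–3 % | 2.5 % / 2 % |
| Uniform, days 1–28 | 0.392 | +0.13 | 1.3 % / 1–2 % | 4.5 % / 5 % |
| Log-normal, median day 15 | 0.343 | +0.43 | 0.9 % / 0.7 % | 6 % / 5 % |

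The nominal rate in each direction is 2.5 %. Simulations used 1,000 to 2,500 trials per setting. The sign follows q: raw stay favours the higher-death arm only if deaths tend to precede typical discharge (q above 0.5).

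**Masking of a true prolongation.** If B survivors stay 10 % longer and deaths fall on days 1–14, Mann–Whitney power to show the longer stay is 55 % at 5 % versus 5 % deaths, 43 % at 5 % versus 8 %, and 34 % at 5 % versus 10 %. With later deaths the loss largely disappears: 57 % to 59 % with deaths on days 1–28, and 56 % to 52 % with median death day 10 (5 % versus 5 %, then 5 % versus 10 %).

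**ICU stay.** Suppose, for illustration, that 30 % of survivors and 80 % of patients who die use the ICU, with the same duration distribution. At 5 % versus 10 % deaths, ICU stay is then significantly longer in the higher-death arm in 12 % of trials and shorter in 0.5 %. Survivors without ICU care score zero, so the direction can be opposite to that for hospital stay.

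**With deaths ranked worst.** At 5 % versus 10 % deaths and equal survivor stays, the higher-death arm was never significantly better in 1,000 trials and was significantly worse in 23 %.

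**The case against.** The strongest reply is that this is a condensed article, that the handling of deaths in length of stay is commonly left to an analysis plan, and that Statistics never names length of stay. Part of this stands: a rule may exist elsewhere, and assigning the continuous-variable rule to stay is a natural reading, not an explicit statement. But the article does state a general rule, and that rule applied as written gives the result above.

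A reader might infer that the arm with more deaths will look better. The documents do not support that. They give no death timing. All-cause mortality is followed to day 28 and 3 months, and Data registration continues follow-up to discharge for patients still in hospital at day 14, so late in-hospital deaths also enter the stay. As the table shows, these can remove or reverse the bias.

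A reader might also infer that an excess of deaths would be hidden. It would not be: mortality is in the primary composite, is analysed as a component, is a secondary outcome at day 28 and 3 months, and is monitored at two interim looks.

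Nor can Kaplan–Meier be called misapplied, since it is tied to no outcome. It would only be a problem if deaths were censored in an analysis of discharge or bowel recovery.

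Finally, days alive and out of hospital to day 28 reach 89 % power at 5 % versus 10 % deaths with 10 % longer survivor stays. That should not be read as recovering a masked stay effect. Most of the gain comes from adding death to the endpoint, which changes the question. Raw stay also answers a fair question about resource use.

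**Conclusion.** The point holds in limited form. The stated rule for continuous variables, applied to length of stay, counts early in-hospital deaths as short stays and is inconsistent with the handling of ventilator-free days. If mortality differs, the comparison mixes stay with death, and the sign depends on timing that the plan does not control.

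The size is modest. At 5 % versus 10 % deaths the mean shift runs from about 0.4 days shorter to 0.4 days longer across the timings tried. The false-benefit rate is about 7 % for deaths on days 1–14, 14 % for very early deaths (median day 3), and nominal or below from a median of day 10 onwards. Larger gaps give larger effects: 46 % at 5 % versus 15 %, and 87 % at 4 % versus 20 %, both with median death day 3. But the protocol cites "4 % in patients undergoing elective noncardiac surgery to 20 % in those undergoing emergency abdominal surgery" as rates for different kinds of surgery, not as a contrast between arms.

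All these figures rest on assumed stay and death-time distributions. The primary outcome, the sample size and the separate mortality analyses are unaffected. Severity: low.

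**What to change.** State the rule before unblinding:

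- Make the between-arm comparison hospital-free days alive to day 28, and likewise ICU-free and HDU-free days alive, by Mann–Whitney. Rank every death by day 28 below any survivor, including a survivor still in hospital on day 28.
- Keep raw length of stay as description only, shown separately for survivors and for patients who died.
- If time to discharge or to bowel recovery is analysed as time-to-event, use cumulative incidence with death as a competing event.

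The cost is a few sentences and derived variables. Data registration already collects the discharge date, lengths of stay in HDU, ICU and ward, and "Survival status (If the patient is deceased, date of death"). Hospital readmission days are not among the listed items, so the definition should say that it counts the index stay unless readmissions are also recorded.

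The downside is small. The measure combines death with stay and is less familiar than days of stay, so mortality and raw stay should be reported beside it to show which of the two drives any difference.

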### Data registration

Data will be entered into the web-based electronic case report form (eCRF) (EOL, Medsharing, Fontenay-sous-Bois, France) by trial or clinical personnel under the supervision of the trial site investigators at each participating center. Data collection will be monitored by trained research coordinators.

The following data will be registered:

Pre-randomization and baseline characteristics: Demographic data (age, height, weight, gender, and body mass index); co-morbidities (hypertension Y/N, renal dysfunction Y/N, chronic heart failure Y/N, diabetes mellitus Y/N, malnutrition Y/N, chronic alcoholism Y/N, and active smoking Y/N); American Society of Anesthesiologists (ASA) physical status; surgical operation for malignancy Y/N; preoperative use of nephrotoxic drugs (NSAIDs) Y/N; preoperative use of angiotensin-converting enzyme inhibitors and/or angiotensin II subtype receptor antagonists Y/N; preoperative administration (type and volume) of intravenous fluids Y/N; preoperative administration (and volume) of blood products Y/N; and routine biological data, including baseline serum creatinine.

At randomization: AKI risk index (class), urgency of surgery (elective or non-elective surgery) (stratification variable).

During the surgical procedure, the following data will be collected:Anesthetic data: type and doses of hypnotics, opioids and muscle relaxants; duration of anesthesia; total volume of maintenance fluid; total volume of trial fluids (aliquots of 250 ml); use (Y/N) and total volume of 0.9 % saline (if volume of trial fluid greater than 30 ml/kg); total number blood products; ventilator settings (tidal volume, PEEP, FiO_2_); baseline (and then hourly) values for bispectral index or entropy; blood pressures (systolic, diastolic and mean) and stroke volume index (SVI); type of hemodynamic monitor (esophageal Doppler Y/N, pulse contour Y/N, other); total number of episodes of hypovolemia; need for administration (Y/N) and infusion rate of vasoactive drugs (ephedrine hydrochloride, noradrenaline, other); and hourly urine output.Surgical data: type of surgery, duration of surgery, surgical technique (laparoscopy Y/N, laparotomy Y/N), total volume of blood losses, and surgical complications Y/N.

From randomization to postoperative Day 1 (07.59 AM): total volume of trial fluids (aliquots of 250 ml); use (Y/N) and total volume of 0.9 % saline (if volume of trial fluid greater than 30 ml/kg); total number blood products and blood losses; need for mechanical invasive- or non-invasive ventilation; hourly values of blood pressures and urine output; need for administration (Y/N); and infusion rate of vasoactive drugs.

Daily from postoperative Day 1 (08.00 AM) to Day 7 after surgery (or hospital discharge):Postoperative care pathway (surgical ward Y/N, HDU Y/N, and ICU Y/N)Epidural analgesia Y/NDaily volume of trial fluid (only on postoperative Day 1) and maintenance fluids including oral and parenteral nutrition, urine output and calculated fluid balanceDaily lowest values for heart rate, blood pressure, peripheral O2 saturation, respiratory rate, temperatureBlood glucose levelResults of samples of plasma creatinine and creatinine clearance, plasma lactate, CRP, bilirubin (standard laboratory values)SIRS scoreKDIGO scoreVariables for SOFA scoring not covered above (until Day 5)Postoperative complications (Y/N, type, and date of diagnosis)Unexpected ICU admission Y/NLength of stay in HDU, ICU, and surgical wardDate of hospital dischargeDeath (Y/N and date)

Fourteen days after surgery:Postoperative complications (Y/N, type, and date of diagnosis)Need for renal replacement therapy on that day Y/N, and total days of RRT (between first and last treatment session)Unexpected ICU admission (Y/N, date of admission)Length of stay in HDU, ICU, surgical wardDate of hospital discharge (as obtained from hospital notes)Survival status (If the patient is deceased, date of death)

If the patient is still present on Day 14, follow up will continue until hospital discharge.

Twenty-eight days after surgery:Postoperative complications (Y/N, type, and date of diagnosis) from Day 14 to Day 28 after surgerySurvival status

Ninety days after surgery:Survival status (if the patient is deceased, date of death)

### Data handling and retention

Data will be handled according to French law. All original records (including consent forms, reports of suspected unexpected serious adverse events, and relevant correspondences) will be archived at the trial sites for 15 years. The clean trial database file will be anonymized and maintained for 15 years.

### Enrollment and timeline

The patients are expected to be included from 20 French university and non-university hospitals during a 2-year period starting in September 2015.

Each participating center has to include two patients per month (holidays excluded) to finish inclusion in 2 years.

2013–2015: Protocol, approvals from ethics committee, and trial tool development (eCRF, randomization system)

2015 to 2017: Inclusion of patients

2017: Cleaning and closure of the database.

Early 2018: Data analyses and writing of the manuscript, and submission for publication.

### Perspectives

Million of patients undergo major abdominal surgery worldwide each year. Inappropriate (excessive or insufficient) perioperative fluid therapy may be associated with significant postoperative complications that adversely affect both short-term and long-term survival and increase the costs of healthcare. Few studies, however, have examined the effects of particular types of fluids (crystalloid or colloid solutions) in surgical patients, and much of the available data are extrapolated from studies in critically ill patients. As far as the investigators are aware, no other large RCTs are assessing the efficacy and safety of 0.9 % saline or 6 % HES with the goal of hemodynamic optimization during major surgery.

